## Abstract

**Background:**

The World Health Organization has set a goal of hepatitis C virus (HCV) elimination by the year 2030. However, no regions in Japan have succeeded in eradicating HCV. Micro-elimination is an approach to attain hepatitis C eradication in which national eradication goals are applied to specific populations so that viral treatment and control efforts can move forward quickly and efficiently. In order to eradicate HCV from Japan, this study aims to achieve HCV micro-elimination in the town of Nagawa.

**Methods and design:**

The Nagawa Project is an ongoing, prospective, multiple-institution, observational study running from April 1, 2021, to March 31, 2024. All residents of Nagawa town, excluding those under 20 years of age, not consenting to the study, or unable to undergo health check-ups due to nursing care needs, will be included. If found to be HCV antibody-positive, the participant will be recommended to see a doctor in consideration of MAC-2 binding protein glycosylation isomer values. Then, the participant will undergo serum HCV RNA measurement with the real-time polymerase chain reaction by an attending physician. If the participant is HCV RNA-positive, he or she will be referred to a hepatologist for further evaluation. In the case of a definitive diagnosis of chronic hepatitis C, direct acting antiviral treatment will be initiated. Through this process, HCV will be systematically micro-eliminated from the region.

**Discussion:**

The Nagawa Project will reveal the prevalence of chronic HCV in addition to the HCV eradication rate in Nagawa town towards achieving HCV micro-elimination.

**Trial registration:**

This study is performed by Shinshu University School of Medicine and was registered as UMIN 000044114 on May 6, 2021.

## Introduction

Hepatitis C is a form of liver disease caused by the hepatitis C virus (HCV). An estimated 71 million people globally and 1 million people in Japan have chronic HCV infection. Chronic infection leads to liver cirrhosis and eventually to hepatocellular carcinoma (HCC) [1], and remains the primary cause of liver cirrhosis and cancer in Japan [2]. However, advances in such therapeutic agents as direct acting antivirals (DAAs), with sustained virological response (SVR) rates of over 95% [3, 4], have reached a stage where it is possible to eliminate HCV entirely.

The World Health Organization (WHO) has announced its commitment to eradicate HCV by the year 2030 via a series of therapeutic measures. However, assuming that high-income countries maintain their current levels of diagnosis and treatment, only 24% are on track to eliminate HCV by 2030, and 60% are off track by at least 20 years [5, 6]. Among developed nations, Japan appears to be on schedule to meet the WHO’s HCV elimination target and should maintain its current levels of HCV diagnosis and treatment. However, improved screening and management remain crucial to ensure the WHO’s goal is met. Specifically, chronic HCV infection is often undiagnosed because it remains largely asymptomatic until the progression to liver cirrhosis or HCC, which highlights the importance of screening and early detection.

In addition to preventing primary and secondary infections, three steps have been outlined to eradicate HCV: 1) Examination to identify HCV-positive individuals through HCV testing, 2) Consultation after encouraging HCV-positive individuals to see hepatologists at medical institutions, and 3) Treatment by eradicating HCV with appropriate DAA interventions. These policies are carried out based on the Basic Act on Hepatitis Measures in Japan. However, from the viewpoint of total HCV eradication, the current rates of HCV testing, medical institution consultations, and treatment may be insufficient; in fact, no region in Japan has successfully eradicated HCV.

"Micro-elimination" is an approach that seeks to quickly and efficiently enable treatment and prevention by applying national-level eradication goals to specific populations, such as certain regions or people with certain demographics [7]. In order to eradicate HCV, it will be important to first perform HCV testing on everyone in a regional cohort (i.e., Examination), then increase the rate of secondary examinations by motivating people testing positive to seek medical advice (Consultation) and receive DAAs (Treatment). Achieving micro-elimination in this way is considered the first step towards eradicating HCV in Japan.

The rural town of Nagawa in the Chiisagata district of Nagano Prefecture (population: 5,903 as of September 1, 2020; mayor: [name]) has been pursuing an aggressive health check-up initiative since May of 1972 under the municipal government’s Children and Health Promotion Division. A system has been created that allows residents to undergo a so-called “Ningen Dock” general health check-up and a metabolic syndrome-specific check-up in alternating years, with certain examinations provided at no cost to the individual. The town’s only public medical institution is Yodakubo Hospital (https://www.yodakubo-hp.jp/), at which all extensive health check-ups are carried out. The metabolic syndrome-specific health check-ups are performed as part of mobile health screenings in every town district with the assistance of the hospital. In addition, many residents with chronic illnesses visit Yodakubo Hospital on a regular basis. Based on the above circumstances, Nagawa town is considered a suitable candidate for the “Nagawa Project” for HCV micro-elimination.

Developed in Japan, MAC-2 binding protein glycosylation isomer (M2BPGi) is a novel serum glycan marker whose secretion from hepatic stellate cells increases with hepatic fibrosis progression [8]. We have described the clinical usefulness of M2BPGi for diagnosing liver fibrosis in chronic liver disease and demonstrated its usefulness as a prognostic biomarker in liver disease and cancer [9–12]. Therefore, the inclusion of M2BPGi results may help in motivating otherwise asymptomatic HCV-positive patients to seek further medical consultation and commence DAA treatment.

The current study has three main goals: 1) complete the screening of all adult residents in Nagawa town and identify the prevalence of HCV RNA-positive individuals, 2) motivate HCV-positive residents to receive consultation at medical institutions with support of M2BPGi findings, and 3) provide DAA intervention and identify the rate of HCV eradication. Ultimately, the Nagawa Project aims to achieve HCV micro-elimination in the town.

## Materials and methods

### Study design

The Nagawa Project is an ongoing, prospective, multiple-institution, observational study that will run from April 1, 2021, to March 31, 2024. The project flowchart is presented in Fig 1. This investigation was reviewed and approved by the Institutional Review Board of Shinshu University School of Medicine (approval number: 4992) on January 5, 2021, and of Yodakubo Hospital (approval number: 2020–8) on January 26, 2021. Both Institutional Review Boards have approved the use of opt-out consent, as described below.

**Fig 1 pone.0256711.g001:**
[figure not shown]
The study flowchart of the Nagawa Project. Abbreviations: HCV, hepatitis C virus; M2BPGi, MAC-2 binding protein glycosylation isomer.

### Ethical statement

All researchers involved in the Nagawa Project will conduct the study in accordance with the Declaration of Helsinki (revised in 2013 by Fortaleza) and the Ethical Guidelines for Medical Research Involving Human Subjects (partially revised on February 28, 2017). An opt-out system is in place for participants in Group A (described below), while written informed consent is obtained from participants in Group B, as shown in Fig 1 and Table 1. All information on the protocol and conduct of the study, including its purpose, is available on the Yodakubo Hospital website (https://www.yodakubo-hp.jp/) and at the hospital reception counter. If patients do not wish to participate in the research, they are freely able to opt out of the study.

**Table 1 pone.0256711.t001:** Method for obtaining blood samples and informed consent in the Nagawa Project.

Group A (vast majority)	Residents taking the “Ningen Dock” health check-up or a metabolic syndrome-specific check at Yodakubo Hospital
	Residents regularly visiting Yodakubo Hospital for a chronic disease or other reason
Blood sample	Remainder of blood serum sample taken for laboratory testing
Informed consent	Opt-out method
Group B (small minority)	Residents with no chance for a health check-up or regular visit to Yodakubo Hospital
Blood sample	Blood serum sample taken on preannounced day at Yodakubo Hospital
Informed consent	Written informed consent

### Target population

#### Inclusion and exclusion criteria

All residents of Nagawa town were initially targeted. Group A (vast majority of residents) consisting of people who undergo the “Ningen Dock” health check-up and the metabolic syndrome-specific check-up at Yodakubo Hospital or patients who regularly visit Yodakubo Hospital for a chronic disease or other reasons and Group B (minority of population) including individuals unable to visit the hospital for the reasons described for Group A above are included. The exclusion criteria are as follows: 1) under 20 years of age, 2) not consenting to the study, and 3) in need of nursing care three or more days per week and unable to receive a health check-up. The remainder of the residents of Nagawa town will be included in the study cohort as shown in Fig 1.

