#### Study endpoints

The first endpoint in this study is determination of the prevalence of chronic hepatitis C patients in Nagawa town. The second endpoint is the rate of HCV elimination in Nagawa town on March 31, 2024.

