### Statistical considerations

#### Sample size estimation

We plan to screen all adult residents in the town of Nagawa (approximately 4500). Since the HCV-positive rate is reportedly 0.35% among workers in Japan [14], it is estimated that approximately 16 people are HCVAb-positive.

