## Discussion

The Nagawa Project is a prospective observational study that will screen all eligible residents for HCV infection and ultimately aims to achieve HCV micro-elimination in the town of Nagawa.

In spite of dramatic advances in DAA treatment for HCV, HCV micro-elimination has yet to be attained in any area of Japan. One possible reason is an unawareness of infection due to the asymptomatic nature of the liver until considerable disease progression, indicating that an HCVAb test is essential to learn of HCV infection. Therefore, in order to achieve micro-elimination, it is essential to establish a system in which all local residents can receive HCV testing. Nagawa town has been actively promoting health check-up services for decades and has established a system that allows residents to receive routine examinations at Yodakubo Hospital. In addition, many residents with chronic diseases visit the hospital on a regular basis. We examined the percentage of Nagawa town residents who had a health check-up or outpatient visit in 2019. Among patients using national health insurance and among the very elderly, the majority had the opportunity for a medical check-up or an outpatient blood test. In the remaining younger cases and residents using employee’s health insurance provided by the Social Health Insurance Unions and the Health Insurance Association of Japan (i.e.: Kyokai Kenpo), at least 46% had a medical check-up at Yodakubo Hospital for a chronic disease, although some residents underwent medical check-ups at other facilities. In our protocol, the township will identify all the residents, and they will be able to receive the test free of charge at their regular medical institutions. For those who do not have regular visits to the hospital, all residents will be given the opportunity to be tested by issuing a request form. Moreover, we offer preannounced days for free blood sample collection at Yodakubo Hospital for this minor population to attain 100% HCVAb testing. In addition, depending on the results, DAA treatment is also available. In order to increase a participating rate of 100%, this study is cooperated with the government of Nagawa town as well as Yodakubo hospital. Nagawa town can identify all its residents by their resident cards and town insurance cards. The insurance card makes it possible to ascertain whether a person has visited a hospital or had an examination. By issuing documents confirming that the residents have been inspected, it is possible to inform residents who have not been inspected and allow those who wish to be inspected to do so. In this way, all adults can be tested.

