
Another possibility is that even if individuals know of their HCV infection, some avoid further consultation and DAA treatment in the absence of symptoms. Of the 1028 people in Nagawa town who underwent health check-ups in 2018, 139 (14%) received the HCVAb test. Three people were HCVAb-positive, among whom only two were recorded as having a secondary evaluation and had already been achieved an SVR by prior antiviral treatment. In order to motivate patients to action, the present study includes M2BPGi measurements to help visualize liver fibrosis stage. M2BPGi is low in healthy individuals and becomes significantly elevated with increasing liver fibrosis, and furthermore is associated with the development of HCC, liver-related complications, and prognosis [15–17]. Therefore, M2BPGi may be useful both as a first-line screening method in health check-ups as well as a motivational tool for suspected patients to undergo secondary screening. In order to achieve HCV eradication nationwide in Japan, more effective tactics will be needed.

Lastly, public awareness campaigns to share information on HCV will be important to maximize the examination and consultation rates. If the examination rate is too low, further information will be provided via the "Koho Nagawa" town publication and on Nagawa town cable television with the assistance of the Nagawa town government. In addition, we will promote the tests conducted in the Nagawa Project via hepatitis medical coordinators in the community. Residents who visit Yodakubo Hospital will also be given information via the hospital’s public relations magazine "Yodakubo Hospital Dayori".

Based on the above mentioned, it is highly likely that micro-elimination in the community can be achieved if this protocol is followed. For the residents of Nagawa town, the HCV test will enable earlier detection and initiation of eradication therapy, which will increase healthy life expectancy. As a downstream effect, this will also contribute to a reduction in future medical costs. In addition, once HCV micro-elimination in Nagawa town is declared, it will create a roadmap and greater opportunity for eliminating HCV in other parts of Nagano Prefecture and across Japan, with the goal of HCV elimination nationwide.

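### Both endpoints, the planned 4500 and the foreseen elimination claim cover all adults of Nagawa town, but the eligibility criteria leave some adults untested

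*Protocol article*

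**What the plan says.** The first goal in the Introduction is to "complete the screening of all adult residents in Nagawa town and identify the prevalence of HCV RNA-positive individuals". The sample size section repeats this reach: "We plan to screen all adult residents in the town of Nagawa (approximately 4500", with about 16 antibody-positive people expected.

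Under Study endpoints, the first endpoint is "determination of the prevalence of chronic hepatitis C patients in Nagawa town". The next sentence reads "The second endpoint is the rate of HCV elimination in Nagawa town on March 31, 2024". Neither is limited to those who are eligible or tested.

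The Discussion describes how the town can find residents who have not been tested and concludes "In this way, all adults can be tested". It later describes what will follow "once HCV micro-elimination in Nagawa town is declared".

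The exclusion criteria remove three groups: people under 20, people who do not consent, and people "in need of nursing care three or more days per week and unable to receive a health check-up". The last two contain adult residents of the town. The statistical analysis section says that the positive rates and the elimination rate will be examined, and ties none of them to the eligible or tested population.

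**The concern.** The population to which the conclusions refer is larger than the population that can be tested. For prevalence, this matters only if untested adults differ from tested ones. For elimination it matters even if they do not, because such a claim is about infection that remains, and untested residents are where undetected infection would remain. With so few positives expected, a small untested group can hold a material part of them.

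A non-consenting adult is also removed from the cohort by definition. A refusal then makes the cohort smaller instead of showing up as a gap in coverage. Coverage of the cohort could look complete while coverage of the town is not.

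**Working it through.** **Inputs from the article.** Adults to be screened: N = 4500. Antibody-positive rate: p = 0.35%, taken from workers in Japan. Both are in the sample size section.

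**The plan's own figure.** N × p = 4500 × 0.0035 = 15.75, or about 16. This reproduces the stated number. It counts every adult, with no deduction for the exclusions. With 5% untested, the tested cohort would be 4275 and the expected count 4275 × 0.0035 = 15.0. With 10% untested, it would be 4050 and 14.2.

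**Assumptions.** The article gives neither the share of adults left untested (f) nor the ratio of their prevalence to that of the tested (r). I take f = 5% and 10%, and r = 0.5, 1 and 3. Tested prevalence is held at 0.35%, and people are treated as independent.

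**Formulas.**
- Expected untested antibody-positives = N × f × r × p
- Chance of at least one = 1 − (1 − r × p)^(N × f)
- Town prevalence = (1 − f) × p + f × r × p
- Relative error of the tested figure = p / town prevalence − 1

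**Worked case, f = 5%, r = 1.** Untested adults: 4500 × 0.05 = 225. Expected positives: 225 × 0.0035 = 0.79. Chance of at least one: 1 − 0.9965^225 = 0.546.

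**Worked case, f = 10%, r = 1.** Untested adults: 450. Expected positives: 450 × 0.0035 = 1.58. Chance of at least one: 1 − 0.9965^450 = 0.794.

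| f | r | Expected untested antibody-positives | Chance of at least one | Town prevalence | Tested figure (0.35%) against town |
|---|---|---|---|---|---|
| 5% | 0.5 | 0.39 | 33% | 0.3413% | 2.6% too high |
| 5% | 1 | 0.79 | 55% | 0.3500% | no error |
| 5% | 3 | 2.36 | 91% | 0.3850% | 9.1% too low |
| 10% | 0.5 | 0.79 | 55% | 0.3325% | 5.3% too high |
| 10% | 1 | 1.58 | 79% | 0.3500% | no error |
| 10% | 3 | 4.73 | 99% | 0.4200% | 16.7% too low |

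**From antibody to infection.** These counts are antibody-positive people, and only some carry virus. If 30% to 70% of them are RNA-positive (assumption), then at r = 1 the chance of at least one untested RNA-positive resident is 1 − (1 − 0.3 × 0.0035)^225 = 21% to 1 − (1 − 0.7 × 0.0035)^225 = 42% for f = 5%. With exponent 450 it is 38% to 67% for f = 10%.

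**The case against.** The other side has good arguments, and several of them limit the point.

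- **Openness and size of the exclusions.** The abstract lists them beside the target population. The care criterion has two conditions, so people in frequent care who can have a check-up stay in. Most residents fall under opt-out consent, which may keep refusals few. All of this stands, and the untested share may be small. Excluding people who refuse is unavoidable, and the point is not that they should be tested.
- **Qualified wording in the Discussion.** Its opening sentence speaks of eligible residents, its 100% figure is an aim, and the sentence about testing all adults can be read as describing opportunity. This also stands. But the qualification does not reach the goal, the planned number, the endpoints or the foreseen declaration.
- **Detail left to other documents.** Denominators and tables are commonly left to an analysis plan, and their absence is not the complaint. The mismatch between the stated endpoints and the stated eligibility lies in the article itself.

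A reader might also infer more than the article supports:

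- *That prevalence will be understated.* This needs higher prevalence among the untested. The article gives no figure for them, does not state their ages, and says that most of the very elderly had a chance of a check-up or blood test. With r below 1 the error reverses.
- *That the plan counts excluded adults as uninfected.* No sentence says so. They are outside the cohort, and the conclusion is then worded for the town.
- *That one missed infection defeats micro-elimination.* The article describes micro-elimination as applying national goals to a defined population and does not equate it with zero infections. The declaration is an outlook in the Discussion, not a decision rule.

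**Conclusion.** The point holds as a mismatch between the population of the claims and the population that is tested. The goal, the planned 4500, both endpoints and the foreseen declaration refer to all adults or to the town, while the eligibility criteria take two groups of adults out.

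For elimination, the consequence needs no difference between tested and untested. At equal prevalence and an assumed untested share of 5% to 10%, the chance that at least one antibody-positive resident is untested is 55% to 79%. For RNA-positive residents it is lower: 21% to 67% over the assumed RNA fractions.

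For prevalence, bias is possible but not shown. Over the assumed range, the tested figure runs from 5.3% above to 16.7% below the town value. All of these sizes rest on assumed f and r and on a worker rate that may not fit this town. The change should be made, but the mismatch does not invalidate the screening itself.

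**What to change.** 1. Word both endpoints as 'among eligible residents who were tested'. Add a town-level version of each with the adult resident register as denominator.
2. Report the excluded and untested adults by age band and sex as 'status unknown'.
3. Give a sensitivity range for residual infections in that group under stated assumed prevalences, for example 0.5 to 3 times that of the tested. A confidence bound cannot replace this, because untested people supply no data and any bound rests on an assumed prevalence.
4. Limit any micro-elimination statement to the screened cohort unless a coverage threshold, fixed before the data are seen, is met.
5. Align the wording on screening or testing all adults in the Introduction, the sample size section and the Discussion with the eligibility criteria.

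The Discussion says the town can already identify all its residents, so the denominator should be available. The cost is some rewording, a small extra analysis and a more cautious headline claim.

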### Collection of blood serum samples (Fig 1 and Table 1)

Group A: The remainder of blood samples (serum) taken for laboratory testing is stored for analysis.Group B: A blood sample will be taken on a preannounced day at Yodakubo Hospital specifically for this population.

#### Trial design and follow-up

Participant registration for the study will run from June 1, 2021, to September 30, 2023. All participants will undergo HCV antibody II (HCVAb) testing (Sysmex Co., Kobe, Japan) and M2BPGi (Sysmex Co., Kobe, Japan) measurement with a HISCL-5000 (Sysmex Co., Kobe, Japan) system using stocked serum. An HCVAb test result ≥1.00 cutoff index (COI) is considered a positive result. M2BPGi readings of <1.00 COI, ≥1.00 COI and <3.00 COI, and ≥3.00 COI, are judged as negative, 1+, and 2+, respectively. Regarding linkage-to-care, if an HCV-positive patient has a high M2BPGi value, this will be used to explain that the risk of cirrhosis and HCC is high at present, and early consultation and treatment will be urged. On the other hand, if M2BPGi is low in an HCV-positive patient, clinicians will make the individual aware of the possibility of progression to cirrhosis and HCC with the onset of fibrosis, at which point M2BPGi will being to rise, and that treatment is crucial to prevent further M2BPGi increases. When the M2BPGi results are returned, an explanatory document with the above descriptions is also given to the participants to encourage them to undergo additional medical examination. The test results will be delivered by mail within two weeks after the analysis. In addition, HCV-positive patients who have not visited the hospital within a few months who receive a health check-up will be encouraged by the town to see a doctor. Such patients who regularly visit Yodakubo Hospital will be recommended by the doctor in charge to see a liver specialist. If the HCVAb test is positive, the participant will be recommended to consult a doctor in consideration of M2BPGi values, at which time serum HCV RNA measurement by the real-time polymerase chain reaction will be performed by an attending physician. If the participant is HCV RNA-positive, he or she will be referred to a hepatologist for further evaluation, whereby a definitive diagnosis of chronic hepatitis C will be ascertained according to diagnostic criteria by the Japan Society of Hepatology [13]. In such cases, DAA treatment will be initiated with patient consent by a hepatologist based on the guidelines of the Japan Society of Hepatology [13]. Patients will be monitored for a SVR every six months to calculate the SVR achievement rate in Nagawa town. Ultimately, the final HCV eradication rate will be determined on March 31, 2024.

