#### Statistical analysis

The HCVAb-positive rate and the HCV RNA-positive rate will be examined. In gender and age comparisons, continuous variables will be statistically evaluated by means of the Mann–Whitney U test, while categorical variables will be analyzed using the chi-square test in order to detect background differences. The HCV elimination rate will be examined at the end of the study.

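### HCV RNA is measured only in antibody-positive residents who choose to consult a doctor, so the first endpoint is unobserved in those who do not attend

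*Protocol article*

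**What the plan says.** The Study endpoints section states: "The first endpoint in this study is determination of the prevalence of chronic hepatitis C patients in Nagawa town". The first goal in the Introduction is worded in terms of viraemia: "complete the screening of all adult residents in Nagawa town and identify the prevalence of HCV RNA-positive individuals". Both are quantities for the whole town.

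The measurement pathway is in Trial design and follow-up. The antibody test is universal among participants: "All participants will undergo HCV antibody II (HCVAb) testing", and it is run on stored serum. The RNA test is not run on that serum. It is tied to a visit, "at which time serum HCV RNA measurement by the real-time polymerase chain reaction will be performed by an attending physician". The visit itself is advised but left to the resident: "If the HCVAb test is positive, the participant will be recommended to consult a doctor in consideration of M2BPGi values". A definitive diagnosis of chronic hepatitis C needs a further step, referral to a hepatologist after a positive RNA result.

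The Statistical analysis section says: "The HCVAb-positive rate and the HCV RNA-positive rate will be examined". It does not say how an antibody-positive resident without an RNA result enters the second rate.

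The Discussion expects some people who know of their infection not to seek follow-up while they have no symptoms. It gives local figures for 2018, when 139 residents had the antibody test: "Three people were HCVAb-positive, among whom only two were recorded as having a secondary evaluation and had already been achieved an SVR".

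**The concern.** An antibody result does not separate current from cleared infection, so the first endpoint depends on the RNA result. That result exists only for antibody-positive residents who act on the recommendation to consult. Non-attendance is also the behaviour that the study's second goal sets out to change, so the design itself treats full attendance as uncertain.

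Attendance is unlikely to be random. The message given to an antibody-positive resident depends on the M2BPGi value and is more urgent when the value is high. Residents who were cured earlier may see no reason to attend. The RNA results in hand may therefore not represent those that are missing.

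The plan expects few antibody-positive residents, so a handful without an RNA result can move the reported prevalence by a large fraction. An analysis plan can bound the effect, but it cannot recover RNA results that were never measured.

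**Working it through.** **Inputs.**
- Adults to be screened: about 4500 (Sample size estimation).
- Assumed positive rate: 0.35% (same section).
- Recorded secondary evaluation in 2018: 2 of 3 antibody-positives (Discussion). The exact 95% interval is 9% to 99%.
- Viraemic share among antibody-positives, r: not in the document. It is assumed to be 50%, with a range of 30% to 70%.
- All 4500 adults are taken as antibody-tested, and antibody-negatives as RNA-negative.

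**The plan's own figure.** 4500 × 0.0035 = 15.75, or about 16 antibody-positives. This reproduces.

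**Formulas.** Let v be the share of antibody-positives with an RNA result, and let attendance be independent of RNA status.
- True prevalence = 16r / 4500.
- Counted prevalence, which is also the lower bound (all unverified negative) = 16vr / 4500.
- Upper bound (all unverified positive) = [16vr + 16(1 − v)] / 4500.
- Relative shortfall of the counted figure = 1 − v, whatever r is.

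**Results per 100,000.**

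| v | r | True | Counted (lower bound) | Upper bound |
|---|---|---|---|---|
| 0.9 | 0.5 | 178 | 160 | 196 |
| 0.8 | 0.5 | 178 | 142 | 213 |
| 2/3 | 0.3 | 107 | 71 | 190 |
| 2/3 | 0.5 | 178 | 119 | 237 |
| 2/3 | 0.7 | 249 | 166 | 284 |
| 0.5 | 0.5 | 178 | 89 | 267 |

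For v = 2/3 and r = 0.5:
- Verified: 16 × 2/3 = 10.67. Unverified: 5.33. Viraemic and verified: 10.67 × 0.5 = 5.33.
- Counted: 5.33/4500 = 119 per 100,000.
- Upper bound: (5.33 + 5.33)/4500 = 237 per 100,000.

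Dropping the unverified from the denominator hardly helps: 5.33/(4500 − 5.33) is still 119 per 100,000. Each unverified person adds 1/4500, or 22 per 100,000, to the distance between the bounds.

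**Scaling up from attenders.** Take r = 0.5, so 8 viraemic and 8 non-viraemic residents and a true prevalence of 178 per 100,000.
- 90% of viraemic and 50% of non-viraemic residents attend: 7.2 and 4.0 are verified. The scaled estimate is 16 × 7.2/11.2 = 10.29, or 229 per 100,000.
- The reverse: 4.0 and 7.2 are verified. The scaled estimate is 16 × 4.0/11.2 = 5.71, or 127 per 100,000.

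**If the 2018 local rate applied.** 4500 × 3/139 = 97 antibody-positives. At two-thirds attendance about 32 would have no RNA result. With only 3 positives the exact 95% interval for that rate is 0.4% to 6.2%.

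**The case against.** The plan does a good deal to raise attendance: results by mail, an explanatory document, encouragement by the town, recommendation by the treating doctor, and publicity. Enrolment closes on September 30, 2023, six months before the final assessment, which leaves time for follow-up. RNA testing at consultation is the care pathway under observation. Rules for missing RNA results commonly stand in a full protocol or analysis plan, and neither is shown. All of this stands, and it limits the point to the measurement pathway and what must be reported from it. It does not make RNA results complete. The article's 100% target concerns participation and antibody testing, not RNA testing.

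Several stronger readings are tempting, but the document does not support them.

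- *That the third antibody-positive person in 2018 was never evaluated.* The text says only that two had a recorded evaluation.
- *That one third is the expected shortfall.* It rests on 2 of 3 people and predates this study's measures. It also requires attendance to be independent of RNA status, which is doubtful here.
- *That Group B positives will be verified least.* The follow-up prompts do name other groups: "HCV-positive patients who have not visited the hospital within a few months who receive a health check-up will be encouraged by the town", while regular hospital visitors are prompted by their doctor. The mailed result and explanatory document, however, go to participants without excluding Group B. Group B members have also come to the hospital and given written consent, so their attendance cannot be ranked.
- *That the elimination rate's denominator shrinks.* No denominator is defined, so this is a possibility only.
- *That the analysis does count non-attenders as negative.* The article does not say how they are handled.

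**Conclusion.** The concern holds in a limited form. As designed, the first endpoint is unobserved in antibody-positive residents who do not consult, and the article itself expects some of them. If they are counted as negative and attendance is independent of RNA status, prevalence is understated by the unverified share. If attendance depends on RNA status, scaling up from attenders can err either way.

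The figure of 119 against a true 178 per 100,000, with bounds of 119 to 237, is an illustration. It rests on 16 antibody-positives, two-thirds attendance from a sample of three, and an assumed viraemic share of 50%. At 80% attendance the bounds would be 142 to 213. With full attendance the problem disappears. The further loss at the hepatologist step is not quantified here.

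**What to change.** **Report the gap and bound it.** State the number of antibody-positive residents without an RNA result. Give RNA-positive prevalence over all tested residents as a lower bound (all of them negative) and an upper bound (all of them positive). This is a change of analysis only. Its price is a wider and less favourable statement of prevalence. Imputation within strata is not advised: about 16 positives leave strata of a few people or none, and the article does not say that prior-treatment history is collected from everyone.

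**Where possible, close the gap.** Measure HCV RNA on the stored serum of antibody-positive participants and use that result for the prevalence endpoint. On the planned figure this is about 16 assays, or about 97 if the 2018 local rate applied. Before that, check that enough serum remains, that it is suitable for RNA testing, and that the opt-out information (Group A) and the written consent (Group B) cover it.

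**Elimination rate.** Say how antibody-positive residents without an RNA result are counted in any elimination rate. This costs one sentence.
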